## Abstract

**Introduction:**

Non-invasive brain stimulation (NIBS) as monotherapy has been increasingly used to enhance the activity of brain networks. However, it is unclear whether a combination of distinct NIBS approaches could enhance prefrontal cortical (PFC) activity.

**Objective:**

We propose to investigate the combined and standalone effects of two NIBS modalities on the PFC through a working memory task, single photon emission computed tomography (SPECT), and salivary cortisol. We hypothesize that the combined protocol will provoke greater changes in the collected measures compared to the remining protocols.

**Methods:**

A randomized, double-blind, sham-controlled, full-factorial design will be conducted. The effects of transcranial direct current stimulation (tDCS) and intermittent theta-burst stimulation (iTBS) will be investigated over four different sessions (sham tDCS + sham iTBS, anodal tDCS + sham iTBS, anodal tDCS + active iTBS and sham tDCS + active iTBS) in 30 healthy adult volunteers. A 99mTc-ethylene cysteine dimer (99mTC-ECD) will be administered during the NIBS session and neuroimaging will be acquired within one hour. Salivary cortisol will be collected before and after each session and an n-back working memory task will be applied after the end of each NIBS session. The outcomes will be cerebral perfusion alterations (99mTC-ECD SPECT), accuracy and reaction time in the n-back task, and changes in salivary cortisol level.

**Conclusion:**

The results from this trial can guide future therapeutic protocols for NIBS treatments stimulating the PFC by demonstrating that the combination of NIBS techniques is feasible, tolerable, and can lead to greater enhancement of PFC activity.

## Introduction

Non-invasive brain stimulation (NIBS) interventions are non-pharmacological and non-psychotherapeutic techniques that use electric currents to treat psychiatric and neurological disorders.^1 , 2^ The main forms of NIBS are repetitive transcranial magnetic stimulation (rTMS) and transcranial direct current stimulation (tDCS). rTMS is based on magnetically-induced fields that are generated from a coil placed over one’s head, causing a discharge of potent electric currents that induce action potentials (APs).^3^ A relatively novel rTMS protocol is called theta-burst stimulation (TBS), which consists of a series of pulses, usually between 3 to 5, at 50 Hz (called a ‘‘burst’’), delivered at a frequency of 5 Hz. This frequency coincides with the theta frequency band of electroencephalography.^2 , 4^ In turn, tDCS uses a low-intensity current delivered to the brain through two electrodes placed on the head. Although tDCS does not generate APs *per se,* its current is capable of modulating cortical excitability towards depolarization (anodal tDCS) or hyperpolarization (cathodal tDCS).^5^

The effects of these NIBS interventions over the dorsolateral prefrontal cortex (DLPFC) have been individually investigated as treatments for several psychiatric conditions and for cognitive enhancement,^6 - 8^ presenting promising results mainly for major depressive disorder (MDD).^9 - 11^ However, the standalone effects of tDCS on cognition and MDD are only moderate.^12 - 14^ Likewise, the moderate effects and cost-benefit profile of rTMS are issues that limit its widespread use as a mainstream treatment modality, leading the field to develop novel personalized approaches.^15^

Based on the rationale that tDCS modulates spontaneous activity via subthreshold alterations of resting membrane potentials, several studies have investigated whether tDCS could potentiate the neural system and thereby enhance the effects of other interventions.^16 , 17^ TDCS applied over the DLPFC combined with other therapies such as antidepressant drugs^18^ and working memory training^19^ have already been evaluated for depression, showing promising results for the combined protocols. Notwithstanding, the effects of tDCS concomitantly applied with different patterns of rTMS (inhibitory and excitatory protocols) have already been investigated over the primary motor cortex (M1) of healthy volunteers.^20 , 21^ These results showed that combined protocols presented greater effects on the amplitude of motor-evoked potentials (towards inhibition and excitation) in comparison to each NIBS technique alone. Besides, to the best of our knowledge only one trial has already evaluated the effects of concomitant application of tDCS and intermittent TBS (iTBS) over the PFC. This study investigated the effects of combined tDCS-iTBS on stress, showing no evidence that combined tDCS-iTBS, compared to iTBS alone, attenuates the psychophysiological stress response in healthy subjects.^22^

Therefore, considering the modest effects of these NIBS techniques as monotherapy and the advances in investigation of combining NIBS therapies, the main aim of this study is to assess the standalone and combined effects of a sub and a suprathreshold NIBS protocol associated with neural facilitation - anodal tDCS and iTBS over the left DLPFC. We propose a phase-I study, with multimodal assessments including 99mTc-ethylene cysteine dimer (ECD) brain SPECT (single photon emission computed tomography), working memory tasks, and salivary cortisol. These three measures were chosen to evaluate direct and indirect PFC functioning, respectively. Regarding the indirect measures, the cognitive task and cortisol levels are associated, respectively, with the PFC cortical-subcortical network and the hypothalamic-pituitary-adrenal (HPA) system, which presents its sensitivity significantly influenced by rTMS effects over the PFC.^23^ Therefore, we hypothesize that the combined protocol will be associated with greater changes in cerebral perfusion, as well as cognitive performance and salivary cortisol levels, than the other protocols (NIBS alone and sham).

## Material and methods

### Design

We propose a phase-I, randomized, double-blind, within-subjects, full-factorial study design, which is efficient for testing the standalone and combined effects of tDCS and iTBS.

### Participants

We will recruit 30 volunteers of both genders, aged from 18 to 45 years, right-handed, and with no prior or present mental or neurological disorders and/or clinical diseases. A pre-screening email will be administered beforehand.

Meeting the pre-screening criteria, each participant will be screened in person for past and/or current psychiatric or neurological diagnoses by trained psychologists with the aid of structured interview questionnaires based on the DSM-5 diagnostic criteria. The evaluators will apply the Portuguese version of the Mini International Neuropsychiatric Interview,^24^ the Hamilton Depression Rating Scale (HAMD),^25^ and the Beck Depression Inventory (BDI),^26^ aiming to investigate, respectively, the presence of any cognitive dysfunction or mood disorders, such as anxiety or depression. The Positive Affect Negative Affect Scale (PANAS)^27^ will also be applied as previous studies suggest that the scale might be a proxy for clinical improvement of depression,^28^ a condition in which the DLPFC is the main target for treatment using NIBS. The self-assessment tool for depression (BDI) will be administered first and further hetero-evaluation (HAMD) will be conducted in order to confirm the emotional state of the participants. Finally, the Edinburgh handedness inventory^29^ will be administered to confirm laterality.

Exclusion criteria are: 1) any contraindication for the techniques to be administered (i.e., tDCS, rTMS, SPECT, and magnetic resonance imaging [MRI]), such as metal implants in the cranial region, including metal plates in the skull and implants in the central nervous system; 2) habitual smokers (more than 10 cigarettes per day), or abuse of/dependence on other drugs; 3) pregnant or planned pregnancy during the study; 4) use of psychoactive drugs, including antidepressant drugs, benzodiazepines and Z-drugs; 5) serious neurological or clinical conditions; 6) conditions that prevent weekly attendance at the service; 7) HAMD score > 7; 8) BDI score > 10.

### Procedure

At the beginning of the study, participants will be screened for participation and asked to give written informed consent. The study is in accordance with the Declaration of Helsinki and was approved by the Ethics Committee at the São Paulo University Hospital das Clínicas (HCFMUSP) and registered on the Plataforma Brasil database (CAAE: 89310918.8.0000.0068).

Participants will be randomized in accordance with a computer-generated list at www.randomizer.org and allocation will be conducted by an assistant not involved in the project. Participants will be asked to come to the research center five times. In line with previous studies of (non)combined NIBS protocols, there will be a one-week interval between the sessions to ensure elimination of carryover effects.^20^ On the first day, all participants will undergo a 3 Tesla MRI (GE, 750W system integrated within a 3.0 Tesla General Electric PET/MRI scanner) scan during which we will acquire T1-weighted and T2-weighted sequences (repetition time [RT] = 1900 ms, echo time [ET] = 2.2 ms, flip angle = 9°, 176 slices/volume, slice thickness = 0.8 mm). MRI acquisition is performed beforehand to target the right and left DLPFC via a neuronavigation system (Brainsight, Rogue Resolutions, Inc). Both left and right DLPFC will be located in each participant by reverse coregistration from the MNI152 stereotaxic coordinates (x - 38, y + 44, z + 26 and x + 38, y + 44, z + 26, respectively) and marked on a cap. This method has been identified as optimal on the basis of clinical outcomes and whole brain functional connectivity.^30 , 31^ After neuronavigation, all other sessions will take place in a well-controlled laboratory environment at the Institute of Psychiatry - HCFMUSP, São Paulo, Brazil. The same procedures will be applied in each of the four sessions, except for neuronavigation, which will only be conducted during the first session.

Before the start of each of the four experimental sessions, participants will be asked to answer a few baseline measurements such as the HAMD, BDI, PANAS, and Hamilton Anxiety Inventory (HAI) and a visual analogue scale (VAS). These will essentially be applied to identify participants’ brain state before the NIBS session and can also serve as potential moderators of the NIBS effects. Afterward, the volunteers’ resting motor threshold^32^ will be determined using a MagVenture device (MagPro X100, Denmark) and a figure of eight coil. Salivary cortisol will be collected after the motor threshold measurement and before venous access is obtained for administration of the 99mTc-ECD radiotracer. After venous access, subjects will undergo a neurostimulation session ( Figure 1A ). First, the tDCS device will be switched on. The tDCS session will last 20 minutes. However, the tDCS protocol will be applied alone for the first eleven minutes and then, for the last 9 minutes of the neurostimulation session, the iTBS protocol over the left DLPFC will be applied concomitantly. The radiotracer (99mTC-ECD) will be injected right after the start of the iTBS protocol ( Figure 1B ).

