**Figure 1 f01:**
[figure not shown]
Protocol that will be applied. A) Sequence of the data acquisition and group allocation. B) Noninvasive brain stimulation protocol. atDCS = anodal transcranial direct current stimulation; AE = adverse effects; iTBS = intermittent Theta-burst stimulation; min = minutes; MRI = magnetic resonance imaging; SPECT = single photon emission computed tomography.

VAS and salivary cortisol will be collected immediately after the end of the session. For the VAS scale, participants will be asked to manually indicate on horizontal 10 cm lines whether they are experiencing any current pain. ‘Zero’ means ‘no pain’ and ‘ten’ means ‘pain as bad as it could possibly be’. To ensure the safety of both NIBS techniques alone and their combination, an Adverse Effects Scale^33^ will be assessed. This scale consists of identifying the produced effects and measuring them on a scale from 1 to 4 points, being 1 – absent, 2 – mild, 3 – moderate and 4 – severe. The working memory task (n-back) will be applied after measurement of adverse effects.

All of the procedures described above will take place at the Institute of Psychiatry - HCFMUSP. However, after the end of the working memory task, the volunteers will be taken to the Nuclear Medicine Center - HCFMUSP, where the SPECT images will be acquired by a trained team.

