### SPECT

Volunteers will be asked to fast 6 hours prior to the SPECT exam. Initially, an injection of the 99mTc-ECD radiotracer with activity of 20 mCi (555 MBq) will be administered during the NIBS session. Images will be acquired up to 60 minutes after administration in SPECT equipment (630 model GE, Milwaukee, WI, USA) consisting of a dual-head gamma camera with dedicated collimator for brain studies (Fan beam). SPECT images will be acquired sequentially with a standardized protocol using a 2.5x zoom factor, 128 x 128 matrix, and acquisition of 240 3/3° projections (two 360° turns) every 20 seconds. The photopic will be centered at 140keV, with a window at 10%. Processing will be performed using an interactive reconstruction method (OSEM) with Butterworth filter, with a cutoff frequency of 0.57, and serial number of 10. The number of interactions used will be 20, with 40 subsets. In addition, we will use the T1 and T2 sequences to correct the data for partial volume effects.

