### Statistical analyses

Sample size was calculated using G*Power 3.1 software.^38^ Since this is an original study and no a-priori power analysis is provided, we estimate a moderate *f* – size effect (0.25). The analysis considered four groups, 4 measurements, correlation between repeated measures of 0.5, alpha of 0.05 and power of 0.85, resulting in a sample size of 28 participants. Considering possible losses, we estimate recruitment of 30 subjects (120 observations).

The Shapiro-Wilk test will be applied to identify the sample distribution. Assuming a normal sample, we will perform analysis of variance (ANOVA) having ‘group’ as independent variable and ‘area of activation’ (observed in the left DLPFC) as dependent variable. The Kruskal-Wallis test will be performed in case of a non-parametric sample. The SPECT images will be available in orthogonal cuts in the transverse, sagittal, and coronal planes (DICOM format). Images will be analyzed using the Statistical Parametric Mapping software (SPM12; Wellcome Department of Imaging Neuroscience, London, UK), executed in Matlab Version 2020 (MathWorks, Natick, MA). We will use SPM to form a statistical map according to the statistical threshold to identify differences among the groups. In-house scripts will be used for partial volume correction procedures based on structural MRI. The SPM images will be subtracted from each group to verify areas of functional activation.

ANOVA or its non-parametric extension will be applied for n-back and salivary cortisol, with ‘group’ as independent variable for both outcomes and ‘cortisol level’ (for salivary cortisol) and accuracy/response time (for working memory performance) as ‘dependent variables’. The associations between n-back task performance (accuracy and response time)/salivary cortisol level and cerebral activation will be estimated with linear regression. We will perform pathway analyses to verify whether cerebral activation is directly associated with the results of working memory performance and cortisol salivary level or is measured by these findings. We will also statistically investigate the possible learning effects of the repetitive application of the working memory task by grouping participants’ scores according to the chronological order of NIBS intervention assignments.

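### Session hour is neither held constant within a participant nor recorded, so time-of-day variation can add noise to the cortisol comparison; a booking rule and one recorded field would limit this

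*Protocol article*

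**What the plan says.** **Timing between sessions.** The Procedure section gives one rule: "there will be a one-week interval between the sessions to ensure elimination of carryover effects". Its stated purpose is carryover.

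**Sameness of sessions.** The same section says "The same procedures will be applied in each of the four sessions, except for neuronavigation", and that "all other sessions will take place in a well-controlled laboratory environment at the Institute of Psychiatry". Both statements concern content and setting; neither names an hour.

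**Fasting.** The SPECT section says "Volunteers will be asked to fast 6 hours prior to the SPECT exam". This is timed from the scan, not from the clock.

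**Saliva samples.** There are two per session. For the first, "Salivary cortisol will be collected after the motor threshold measurement and before venous access is obtained". For the second, in the text after Figure 1, "VAS and salivary cortisol will be collected immediately after the end of the session". The Salivary cortisol section then specifies the swab, centrifugation, storage and assay. It does not mention the time of sampling.

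**Outcome and analysis.** The abstract lists the outcome as "changes in salivary cortisol level". The Statistical analyses section says "ANOVA or its non-parametric extension will be applied for n-back and salivary cortisol", with group as the independent variable and cortisol level as the dependent variable. It names neither a baseline term nor a time-of-day term for cortisol.

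**The concern.** Cortisol is one of three outcome domains, alongside perfusion and working memory. Each participant is compared with themselves over four visits, and cortisol also enters the regression and pathway analyses with cerebral activation. Cortisol varies over the day. If one participant's sessions fall at different hours, that variation becomes part of the within-person error against which the four conditions are tested.

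The article names other nuisance factors that it intends to examine: order and learning for the n-back task, and mood shifts between sessions. Time of day is not among them. If sampling times are neither held nor recorded, the analyst cannot adjust for them afterwards. What is at stake is precision for the cortisol comparison and for its association with perfusion.

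**Working it through.** **Inputs from the Statistical analyses section.** f = 0.25, four groups, m = 4 measurements, correlation ρ = 0.5, α = 0.05, target power 0.85, result 28 participants, 30 to be recruited.

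**Step 1: reproduce the plan's figure.** For a within-subject factor in repeated-measures ANOVA, with sphericity:

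λ = f² × N × m / (1 − ρ), with df1 = m − 1 and df2 = (N − g)(m − 1), where g is the number of groups entered.

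- N = 28: λ = 0.0625 × 28 × 4 / 0.5 = 14. With g = 4 (df 3 and 72), power is 0.878. Stepping N in multiples of 4, 28 is the smallest size that reaches 0.85, so the plan's figure reproduces.
- With g = 1, which suits a design where everyone receives all four conditions (df 3 and 81), power at N = 28 is 0.880.
- N = 30: λ = 0.0625 × 30 × 4 / 0.5 = 15. With g = 1 (df 3 and 87), power is 0.904.

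**Step 2: add time-of-day variance.** Set the total variance to 1, so the within-person part is 1 − ρ = 0.5. Let hour of session add a share s of that part and hold the raw effect fixed:

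λ(s) = f² × N × m / [0.5 × (1 + s)]

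For example, at N = 30 and s = 0.20, λ = 15 / 1.2 = 12.5. **The values of s are assumptions**, since the article gives no cortisol variance. Results with g = 1:

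| Extra within-person variance s | Power, N = 28 | Power, N = 30 |
|---|---|---|
| 0% | 0.880 | 0.904 |
| 10% | 0.844 | 0.872 |
| 20% | 0.808 | 0.839 |
| 50% | 0.706 | 0.740 |
| 100% | 0.567 | 0.601 |

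**Step 3: find the threshold.** Solving for power = 0.85 gives s = 8.4% at N = 28 and s = 16.6% at N = 30 (7.8% and 16.0% with g = 4). As a ratio of SDs, these are √0.084 ≈ 0.29 and √0.166 ≈ 0.41 of the within-person residual SD. The implied correlation falls from 0.5 to about 0.48 and 0.46. To keep 0.85, the sample would need to be 31, 39 or 51 for s = 20%, 50% or 100%.

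**Step 4: see what the pre-session sample does.** Let h be the hour-related shift in level, τ the stimulation effect and e1, e2 the remaining errors:

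- pre = μ + h + e1
- post = μ + h + τ + d(h) + e2
- post − pre = τ + d(h) + e2 − e1

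Here d(h) is the drift over the short gap between samples, which may depend on the hour. The common shift h cancels in the change; only d(h) remains. Step 2 therefore describes an analysis of one post-session level per condition. For pre-post change, the hour-related contribution is smaller, but the article gives nothing from which to quantify it.

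**The case against.** **The article is condensed.** A booking window and a sampling-time field may be in the full protocol or an operating manual, and Figure 1A, which shows the acquisition sequence, is not available here. This stands as a caveat: if the rule exists there, that part of the point is already met. Against it, the article goes down to swab material, assay supplier, screen size and viewing distance, and lists the between-session factors it will examine, yet is silent on hour.

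**The pre-session sample may be used.** The abstract defines the outcome as change and both samples are scheduled, so cortisol level may be only a short label. This stands in part. The Statistical analyses section names level and no baseline term; the two statements leave the analysed quantity open, and the size of the problem depends on it.

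**A reader might infer that cortisol power is cut below 0.85.** The documents do not show this. The 0.85 comes from one generic f and ρ tied to no particular outcome. The design starts at 0.88 to 0.90, no time-of-day variance is given, and ρ = 0.5 may already include some ordinary session-to-session variation, in which case adding more would count it twice.

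**A reader might also infer bias, or a false stimulation effect from chance differences in hour.** That does not follow either. Condition order is randomized and counter-balanced, so hour differences unrelated to condition are ordinary error, already covered by the 5% test level.

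**Conclusion.** The point holds as one about precision. The article as written does not keep a participant's sessions at the same hour, does not provide for recording sampling time, and names neither a baseline nor a time term in the cortisol analysis. Time-of-day variation can therefore inflate the within-person cortisol error.

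The threshold is low but conditional: more than about 8% extra within-person variance with 28 participants, or about 17% with 30, would take power below 0.85. This assumes the plan's f = 0.25 and ρ = 0.5 apply to cortisol, that ρ does not already contain the hour-related noise, and that a single post-session level is analysed. With pre-post change the loss is smaller. Whether the threshold is crossed cannot be settled from the article. The point ranks as a cheap improvement, not as a flaw that threatens the trial's conclusions.

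**What to change.** 1. Book each participant's four sessions within the same clock window, at whatever hour suits the site (for example, start times within one hour of that person's first session).
2. Record the clock time of every saliva sample.
3. State that post-session cortisol is analysed with adjustment for the same session's pre-session sample and for sampling time, in a model that respects the repeated measures within participant. This also settles whether level or change is meant.

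The cost is a booking rule, one recorded field and a sentence in the analysis section, with no added visits, staff or participants. The downside is less freedom in scheduling with the nuclear medicine centre. Items 1 and 2 must be in place before data collection, because unrecorded times cannot be reconstructed. If the full protocol already contains them, only item 3 is needed.
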